## Abstract

**Background**: Rising costs and demands for improved quality of care present complex challenges for existing healthcare systems. The strain on healthcare resources is exacerbated by the increasing complexity of patient conditions. The Diagnosis-Related Group (DRG) system classifies inpatients according to clinical and treatment criteria, controls healthcare expenditures, and ensures the sustainability of procedures. The cost of nursing care is included in the DRG system in the same way as other fixed costs of hospital care, but the amount of nursing care provided for the same DRG can vary widely. This study, which is based on this protocol, will aim to assess the variability of nursing costs within and across DRGs and to measure how much variability in nursing care is explained by DRGs by comparing nursing care delivery in acute care hospitals with the DRG reimbursement system in Italy. It is necessary to develop a specific protocol to ensure systematic and consistent data collection at the national level. **Methods**: A multicenter retrospective cross-sectional study will be conducted. A random sample of five public Italian hospitals will be enrolled. Patients included in medical or surgical DRGs, hospitalized and discharged in 2022 will be included. Data will be collected retrospectively from two sources: hospital discharge records and nursing records. Inferential statistics will be used to assess the variability of nursing time and costs across hospitals and DRGs. Nursing costs will be determined by several factors, including time spent on nursing activities and the hourly wages of nursing staff. The time needed to complete each activity will be estimated by a convenience sample of nurses from the hospitals included in this study. The annual salary of nurses will be used to calculate the nursing cost per minute, multipled by the amount of time spent per each nursing activity. The cost per patient per day of hospitalization will be calculated. **Conclusions**: The results of this study will shed light on the variation in nursing care across different DRGs. This understanding will guide recommendations for optimizing healthcare resource allocation and enhancing the efficiency of the DRG system in Italy.

## 1. Introduction

The current healthcare system is facing a complex challenge, with rising costs and the need for improved quality of care [1]. This is exacerbated by the growing complexity of patient conditions, particularly chronic illnesses and an aging population, which put pressure on healthcare systems [2].

To maintain the sustainability of public finances, it is crucial to monitor public health expenditure. Governments reimburse health service expenditure through specific reimbursement systems, such as the Diagnosis-Related Group (DRG) system. The DRG system was created to maintain sustainable inpatient procedures, control healthcare costs, and categorize inpatients based on clinical and treatment criteria. Patients in the same group are expected to use similar resources, encouraging clinicians to effectively manage costs [3,4]. However, this system does not include the costs of nursing care [5].

Nurses are the largest professional group in the healthcare system. However, very little is known about the cost and quality of nursing care, and more specifically, the effectiveness of the care provided by each nurse [5]. In almost all countries, nursing care costs are considered a service cost and are included in the DRG system, similarly to hospitals’ other fixed costs [3]. The DRG system estimates the cost of hospital nursing care based on the total number of nurses assigned to inpatients. Consequently, nursing care costs are calculated as an average lump sum that does not take into account care intensity, the level of patient dependency, the variability in nursing resource consumption, and the intrinsic and intangible characteristics of nursing care [6]. This implies that the amount of nursing care may vary considerably even within the same DRG [7].

Previous studies have contributed to the definition of new reimbursement models in the attempt to highlight the cost weights of nursing care [7,8,9,10]. In the payment rate formulation process theorized by Knauf [7], nursing costs were assigned to each DRG based on nursing intensity weights (NIWs). This model was developed using a Delphi approach and was capable of interpreting the quantity and types of nursing activities provided to patients. Welton and colleagues tested the ‘nursing intensity billing model’ by establishing a fixed nursing weight per diem for nursing intensity (i.e., nursing hours and costs). The results highlighted that the addition of a single nursing component that was not previously included in inpatient reimbursement systems improved hospital payment accuracy. Dykes and colleagues estimated the time spent on nursing activities through relative value units (RVUs) using nursing assessment data from the electronic health record (EHR) [8]. Time-Based Activity Driven (TBAD) costing is an alternative micro-costing method developed by Kaplan and colleagues [9], which evaluated the amount of time spent in key nursing activities across the care cycle (both clinical and administrative). Sermeus and colleagues [10] theorized a reimbursement model called ‘Nursing Minimum Dataset II’ (NMDSII), which accounts for nursing resource weights by measuring the time and frequency of the nursing activities performed. Other authors have studied other variables that contribute to assessing the weight of nursing care. Griffiths and colleagues [11], for example, evaluated the impact of staffing models on patient outcomes. Staffing models with higher baseline rosters increased costs but led to better outcomes (i.e., reduction in mortality and lengths of stay). Jenkins and Welton [12] pointed out that patient severity was associated with an increase in costs and nursing intensity, while nursing experience did not significantly increase the cost of care activities.

Although several models for adequately evaluating nursing costs have been theorized, the results of these studies are still preliminary [5] and a definitive model assessing the cost weight and effectiveness of nursing care is unavailable.

In Italy, there are currently no studies that have shown whether the inclusion of nursing data in the reimbursement systems of healthcare services can contribute to a more equitable distribution of healthcare financial resources. The study based on this protocol will aim to fill this gap by examining the costs related to nursing activities within the DRG reimbursement system. The findings could clarify the variability in nursing costs provided within the same DRG, offering insights on how to better align DRG reimbursements with actual nursing care costs. Achieving this alignment may involve adjusting the DRG cost weights to account for nursing care or establishing a separate nursing intensity weight for each DRG category. Moreover, the results could help develop a replicable framework in this and other settings for assessing nursing costs and quality of care and further examine the relationship between care, patient outcomes, and healthcare costs.

## 2. Materials and Methods

### 2.1. Aims

The primary aims of this study are (1) to assess the variability of nursing costs between different DRGs and within the same DRG; and (2) to measure how much variability in the intensity of nursing care is explained by DRGs.

The secondary objectives of this study are (1) to measure the amount of nursing activity in acute care hospitals; (2) to examine the variability of the intensity of nursing care activities by DRG within patients and across patients controlling for hospital and region; and (3) to identify and quantify any differences in care needs among patients discharged with the same DRG.

### 2.2. Study Design

A multicenter retrospective cross-sectional study will be conducted. A convenience sample of all patients admitted and discharged in the year 2022 will be collected. Data will be collected retrospectively from two sources: (1) hospital discharge records and (2) nursing records. Retrospective data collection will offer a comprehensive picture of the nursing care delivered, as well as the possible heterogeneity of information on nursing activities provided by various healthcare institutions. The discharge records will be used to extract patient demographic data (e.g., gender, residency) and clinical data (e.g., diagnosis, diagnostic procedures performed, and length of stay). Nursing care activities (i.e., frequency and type) will be collected from nursing records. These data will be extracted from the EHR systems of each participating hospital.

### 2.3. Study Setting

A random sample of 5 public acute hospitals will be selected from the total number of potentially eligible hospitals that have expressed interest in participating in this study. To ensure representativeness across Italy, one hospital will be chosen from each geographical area identified according to the classification of the Italian National Institute of Statistics (ISTAT):Northwest (Liguria, Lombardia, Piemonte, and Valle d’Aosta);Northeast (Emilia-Romagna, Friuli-Venezia Giulia, Trentino-Alto Adige, and Veneto);Central (Lazio, Marche, Tuscany, and Umbria);South (Abruzzo, Basilicata, Calabria, Campania, Molise, and Puglia);Islands (Sicily and Sardegna).

To ensure randomization when selecting the sample of hospitals, a comprehensive list of all public hospitals that expressed interest in participating in this study across the five geographical areas of Italy will be created. Then, we will use stratified random sampling to randomly select one hospital from each area, employing a random number generator to eliminate bias.

### 2.4. Eligibility Criteria for Hospitals

The list of Italian hospitals published by the Ministry of Health [13] will be consulted. To be eligible for enrolment, hospitals need to meet the following inclusion criteria: (1) have more than 200 beds; (2) be a public hospital; (3) have at least two wards belonging to medical and surgical departments; (4) provide written consent to participate in the study; and (5) have had an electronic nursing documentation system in place since 1 January 2022. Only medical and surgical departments will be considered, as we expect greater variability in nursing activities per DRG in these settings. Clinical units that treat acute conditions for less than one day, such as emergency rooms and day hospital wards, as well as maternity units, will be excluded. Healthcare services listed by the Ministry of Health as nursing homes or rehabilitation facilities will also be excluded from this study.

### 2.5. Eligibility Criteria for Patients

All data regarding included patients admitted and discharged in the year 2022 will be collected. Data will be collected from patients who meet the following inclusion criteria: (a) patients with medical or surgical DRGs (selected by the department code on the hospital discharge form) with a length of stay > 1 day; (b) patients whose admission and discharge took place in the same ward; and (c) patients admitted and discharged in 2022. Patients aged < 18 years will be excluded.

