### 2.7. Procedures

This study started in January 2024 and is planned to end in March 2025. First, a pilot study was conducted to assess the characteristics of the EHR in the enrolled hospitals. Given the lack of a unique national electronic system for storing health information, heterogeneity in the collection and organization of the nursing activities is expected. Therefore, a preliminary meeting was organized with the nursing directors of each hospital. During this meeting, nursing directors described the EHR used in their hospitals. From this information, an electronic dataset was prepared to allow each hospital to enter information on nursing care activities. For each hospital, two medical and two surgical wards will be considered for enrolment. If there are more than two medical/surgical wards in the same department, the two wards with the highest number of patients admitted during the study period will be selected.

Eligible patients will be enrolled by searching the EHR. Data will be collected retrospectively to gather information on nursing care provided in 2022. This study will collect data from all patients included in medical or surgical DRGs. All nursing activities performed on these patients and documented in the EHR will be considered.

Within each hospital, a procedural manager will be designated to extract and de-identify data of interest. The data of patients who meet the inclusion criteria will be transmitted to the principal investigator (PI) by uploading the data into a secure server specific for this study. The upload will take place via a dedicated cloud platform established on an ad hoc basis for the project, allowing each local investigator of the participating centers to access and provide data.

For login purposes, each local investigator will have a username and password (which can be modified by the user after the initial login). Each local investigator will only have access to his or her own uploaded data, while the principal investigator will have access to all the data submitted by each participating center. The Italian Regulatory Board for Nursing Professions (FNOPI) owns the server where the data will be kept. Data gathering will be continuously evaluated, and all disaster recovery measures will be in place. Figure 1 summarizes the steps of the study.

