### 2.9. Source of Bias

The potential sources of bias in this study will include selection bias due to the proposed convenience sample, which will consist of five public hospitals in Italy. However, we expect to collect a substantial amount of data from patients across all geographical areas of Italy, with an estimated sample size of at least 15,000 individuals. Data collection bias may also arise from retrospective data collection, where incomplete records could affect the results, leading to inconsistencies in estimating the amount of nursing activities digitally registered and the related nursing costs. This bias will be controlled by performing multiple data imputation. Contextual biases related to institutional policies and healthcare culture may also influence nursing practices and patient care across different hospitals. Therefore, a thorough examination of institutional policies and healthcare cultures will be required to address contextual biases during data analysis. A potential source of bias is that the estimated nursing costs are based on a convenience sample of nurse estimates. This approach may not accurately capture the variability in nursing care across different settings. As a result, there is a risk of either overestimating or underestimating nursing costs, depending on how accurately nurses report the time spent on various activities. Thus, the development of standardized data collection guidelines, and the provision of comprehensive training for staff, will be essential to ensure consistency and accuracy in records, thereby minimizing measurement bias related to the reporting of nursing activity time. Finally, the implementation of ongoing evaluation and feedback mechanisms will further help identify and correct biases throughout the research process.

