## 3. Limitations

The limitations of the study may be related to the number of missing data from nursing records, as the data will be collected from hospitals with different nursing record systems. This could lead to sampling bias. However, appropriate handling of missing data (e.g., multiple imputation) will be considered to reduce this bias. Another limitation could be related to the choice of including a limited number of acute care wards of five hospitals in this study, without adjusting for differences in hospital size. This may limit the representativeness of the findings, as the results may not fully reflect the broader population of Italian Hospitals. However, the inclusion criteria were carefully assessed to guarantee both the feasibility of this study and the generalizability of the results. Moreover, it should be considered that this will be the first descriptive study that will present a picture of existing differences in nursing costs between different DRGs and within the same DRGs. Finally, the study’s cross-sectional design, which focuses on patients admitted and discharged during 2022, represents another limitation.

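### The same-ward and 2022-to-2022 rules select stays on features plausibly tied to nursing need; the same-ward rule is not disclosed as a limitation, yet the criteria are said to guarantee generalizability

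*Protocol article*

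**What the plan says.** The primary aims (section 2.1) are "to assess the variability of nursing costs between different DRGs and within the same DRG" and "to measure how much variability in the intensity of nursing care is explained by DRGs". Table 1 shows that the DRG is assigned per admission.

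Section 2.5 sets three patient rules that bear on this: a medical or surgical DRG "with a length of stay > 1 day"; "patients whose admission and discharge took place in the same ward"; and "patients admitted and discharged in 2022". No reason is given for the same-ward rule.

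Section 2.8 builds the cost of a patient's care from activity times, activity counts, wages and devices, and then expresses it per day of hospitalization so that stays of different length can be compared.

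Section 2.9 names "selection bias due to the proposed convenience sample, which will consist of five public hospitals in Italy" and answers it with an expected 15,000 or more patients. Section 3 concedes that few wards and few hospitals may limit representativeness, and lists the 2022 window as a further limitation without mentioning the loss of long stays. It also says the inclusion criteria were assessed "to guarantee both the feasibility of this study and the generalizability of the results". Neither section names the same-ward rule.

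Under sections 2.7 and 2.10, hospitals transmit data only for patients who meet the criteria.

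**The concern.** The primary quantity is a spread: how much nursing cost differs among patients who share a DRG. An eligibility rule that depends on something related to nursing need changes that spread directly. Moving to another ward and staying a long time are both plausible markers of need, so both rules condition on something close to the outcome.

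The same-ward rule matters more. It is undisclosed and, because only included patients' data leave the hospital, its effect could not be examined afterwards from the study database. Section 2.7 also says data come from all patients in medical or surgical DRGs, which a reader may take at face value.

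The wording leaves a second gap. It compares only the first and last ward, so a stay that went elsewhere and came back qualifies. The article does not say whether activities elsewhere are counted, or whether those days stay in the per-day denominator.

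The results are meant to inform DRG weights and to go to policy-makers (sections 1 and 4), so it matters which stays they describe.

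**Working it through.** The document gives no transfer share, length-of-stay distribution or within-DRG standard deviation. Those inputs are assumed below and shown over a range. The only stated figure is the expected sample of at least 15,000. It has no power calculation behind it to reproduce; with 5 hospitals and 4 wards each it means 15,000 / 20 = 750 stays per ward.

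**1. Year rule, by length of stay.** With admissions spread evenly over 365 days, a stay of L days runs into 2023 with probability L/365.

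| L (days) | Lost |
|---|---|
| 5 | 1.4% |
| 10 | 2.7% |
| 30 | 8.2% |
| 60 | 16.4% |
| 90 | 24.7% |

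The rule thins long stays; it does not cut them off.

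**2. Year rule, overall.** Assume lognormal stays longer than 1 day, each weighted by 1 − L/365 (simulation, 4 million draws).

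| Mean, CV | Stays lost | Variance of length of stay retained |
|---|---|---|
| 6 days, 0.7 | 1.65% | 0.97 |
| 8 days, 0.8 | 2.20% | 0.95 |
| 8 days, 1.0 | 2.23% | 0.91 |
| 10 days, 1.0 | 2.76% | 0.88 |
| 12 days, 1.2 | 3.33% | 0.79 |

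If 15,000 is the number retained, the stays lost are 15,000 × 0.0165 / 0.9835 ≈ 250 to 15,000 × 0.0333 / 0.9667 ≈ 520. The last column applies to length of stay, and to whole-stay cost so far as cost follows length. It does not apply to cost per day.

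**3. Same-ward rule.** Let p be the share of a DRG's stays that end in another ward, d their mean shift in standard deviations of the retained stays, and r their SD ratio. Then

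retained / full variance = 1 / [(1 − p) + p r² + p(1 − p) d²].

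- d = 0, r = 1, any p: 1.00.
- p = 0.10, d = 0.5, r = 1: 1 / 1.0225 = 0.98.
- p = 0.10, d = 1, r = 1.5: 1 / (0.9 + 0.225 + 0.09) = 0.82.
- p = 0.20, d = 1, r = 1.5: 1 / (0.8 + 0.45 + 0.16) = 0.71.

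With a common CV of 0.6 and a cost ratio k, d = (k − 1) / 0.6 and r = k. At p = 0.10:

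- k = 1.2: 1 / (0.9 + 0.144 + 0.01) = 0.95.
- k = 0.8: 1 / (0.9 + 0.064 + 0.01) = 1.03.

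If transferred stays cost less per day than the others, the retained variance is therefore slightly too large, not too small.

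**4. Consequence for aim 2.** Let v be the within-DRG variance ratio, with between-DRG variance unchanged. A true explained share R² becomes R² / [R² + (1 − R²)v]. For R² = 0.40:

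- v = 0.9: 0.40 / 0.94 = 0.43.
- v = 0.8: 0.40 / 0.88 = 0.45.
- v = 1.03: 0.40 / 1.018 = 0.39.

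If transfer shares differ between DRGs, the between-DRG variance moves as well, and the direction is open again.

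**The case against.** The strongest reply is that the per-day scale in section 2.8 exists to make stays of different length comparable. Losing long stays narrows the distribution of length, but need not narrow cost per day. This stands: a downward bias on that scale is not shown. It does not remove the concern for whole-stay cost, nor the possibility of bias in either direction per day.

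The year rule is also small overall, and section 3 names the 2022 window. That stands too, so the year rule is the lesser part. The expected 15,000 in section 2.9 answers bias from the choice of hospitals, not from the patient rules, and section 3 does concede limited representativeness. The conflict is therefore with one sentence on generalizability and with silence on the same-ward rule.

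Three stronger readings are tempting and are not supported:

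- *Ward choice also favours short stays*, because "the two wards with the highest number of patients admitted during the study period will be selected". Admissions equal beds × occupancy × 365 / mean stay. At an assumed 90% occupancy, 20 beds at 6 days and 40 beds at 12 days both give 1,095. The document gives no ward sizes or case mix, and the rule applies only where a department has more than two wards.
- *Much of the within-DRG variance is lost.* That needs an assumed two- to three-fold cost for transferred stays, for which the document offers no basis.
- *The estimated variability is a lower bound for all stays.* Step 3 shows that the sign can reverse.

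The mismatch for stays that leave and return is also not established: section 2.7 counts all documented nursing activity for included patients, which may cover time in other units. The text leaves this open.

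**Conclusion.** The point holds as one of selection and disclosure. The same-ward rule removes every stay ending in another ward, is given no reason and is not listed as a limitation. The year rule loses stays in proportion to their length, about 1.7% to 3.3% overall under the assumed distributions and even admissions.

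If the removed stays differ in nursing need, both primary results are biased, most clearly for whole-stay cost. Over the assumed range the same-ward rule leaves between about 0.71 and 1.03 of the true within-DRG variance. The lower values need transferred stays to be both costlier and more variable. For cost per day the document fixes neither sign nor size.

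A guarantee of generalizability is not a property of this design. Because data on excluded stays do not reach the study team, the plan as written could not show whether the exclusion matters.

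**What to change.** 1. Replace the 2022-to-2022 rule in section 2.5 with all admissions from 1 January to 31 December 2022, followed to discharge, including discharge in 2023. This fits the requirement of electronic nursing records from 1 January 2022. The study began in January 2024, so nearly all these stays would already have ended.
2. Have each hospital supply, from its own discharge records, a de-identified aggregate table of the stays excluded by the same-ward rule, by DRG, age, CIRS and length of stay. Compare it with the included stays. The study database does not hold these data, so the table must be requested.
3. State whether a stay that left the ward and returned qualifies. Make the activities counted and the days in the per-day denominator cover the same period.
4. In section 3, list the same-ward rule as a limitation, give its reason, and replace the guarantee with a claim limited to stays admitted to and discharged from the same ward.

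The cost is a short extra extract into 2023, one aggregate table per hospital, and a narrower claim.
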